#### Adverse Events

Participants will be asked about adverse experiences at each massage visit and during the 10-week telephone interviews. We will define an adverse experience as any unfavorable and unintended sign, symptom or disease temporally associated with the use of the massage treatments that could reasonably be related to the treatments. Because massage has relatively short-term physiological effects, we will not report adverse events that first manifest more than one week after a participant's final treatment (or more than 10 weeks after randomization for the usual care control group). If a participant develops a Serious Adverse Experience (i.e., any adverse event occurring during treatment that results in any of the following outcomes: death, a life-threatening adverse event, inpatient hospitalization or prolongation of existing hospitalization, a persistent or significant disability/incapacity, or cancer) during the 10 weeks after randomization, it will be promptly (within 7 days) reported to the chair of the Data Safety Monitoring Body. If the Adverse Experience is, at least possibly, due to massage, it will also be promptly reported to the Group Health IRB and to NCCAM's Office of Clinical and Regulatory Affairs. In addition, we will summarize all adverse experiences in the trial in our routine reports to our DSMB and IRB.

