#### Stopping rules

The trial will be stopped only if the Data Safety Monitoring Body (DSMB) believes there is an unacceptable risk of serious adverse events in one or more of the treatment arms. In this case, the DSMB could decide to terminate one of the arms of the trial or the entire trial.

We are not proposing to perform an interim analysis for efficacy and therefore have established no formal stopping rules. Even if the two massage treatments reduce pain and dysfunction (the primary outcomes of this trial) more than usual care, we do not consider this an important enough reason to end the trial early. Previous trials of massage have been plagued by small sample sizes and we think it is important that this study be large enough and long enough to clearly evaluate the effectiveness of massage.

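### The adverse-experience definition excludes the usual-care arm that it also sets a window for, and prompt serious-event reporting ends about a week before the massage adverse-event window

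*Protocol article*

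**What the plan says.** All the rules at issue are in the protocol article, most of them in its Adverse Events section.

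- **Definition.** An adverse experience is an unfavourable, unintended event "temporally associated with the use of the massage treatments that could reasonably be related to the treatments".
- **Serious events.** These are "any adverse event occurring during treatment that results in any of the following outcomes", followed by a list such as death, hospitalisation and lasting disability.
- **Window, massage arms.** "we will not report adverse events that first manifest more than one week after a participant's final treatment".
- **Window, usual care.** The same sentence continues in parentheses: "or more than 10 weeks after randomization for the usual care control group".
- **Prompt report to the DSMB.** This applies if a serious event develops "during the 10 weeks after randomization, it will be promptly (within 7 days) reported to the chair of the Data Safety Monitoring Body".
- **IRB and NCCAM.** "If the Adverse Experience is, at least possibly, due to massage, it will also be promptly reported to the Group Health IRB", and likewise to NCCAM.
- **Enquiry.** "Participants will be asked about adverse experiences at each massage visit and during the 10-week telephone interviews". Table 3 marks adverse experiences at the 10-week interview only and does not limit that row to the massage arms, although it does limit another row to them.
- **Routine reports.** The section ends by committing to summarise all adverse experiences for the DSMB and IRB.

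Under Stopping rules, the trial ends early only if the DSMB "believes there is an unacceptable risk of serious adverse events in one or more of the treatment arms".

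**The concern.** Two sets of rules do not fit together.

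First, relation to massage is part of what makes an event an adverse experience. Usual-care participants receive no study massage, so the definition leaves nothing to report in the window set for them. The later causality step is hard to explain as well: if every adverse experience is already one that could reasonably be related to massage, a test for possible relation has little left to separate. Staff following the text cannot tell whether an unrelated hospitalisation, in any arm, should be logged or sent to the DSMB chair.

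Second, the two reporting periods have different origins. The massage window runs from the last treatment and the prompt serious-event window runs from randomisation. If the first ends later, serious events in its final days count as reportable but fall outside the 7-day route.

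At stake is the safety information given to the DSMB, whose view of serious risk is the only stated ground for stopping the trial early. No efficacy analysis is affected.

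**Working it through.** **1. The definition against the other rules**

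| Rule | Usual-care event | Unrelated massage-arm event |
|---|---|---|
| Adverse-experience definition | excluded | excluded |
| Serious definition (during treatment) | excluded, as there is no study treatment | included only if read as independent of the first definition |
| Reporting window | included, 10 weeks | included, to one week after last treatment |
| Table 3 question | asked at week 10 | asked at week 10 |
| IRB/NCCAM causality test | has a function only if unrelated events were recorded | same |

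The first row excludes what the last three presuppose. The windows, the table and the causality step make sense only if events are collected in every arm whatever their cause.

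**2. The two windows on the nominal schedule**

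Inputs: the follow-up year is 52 weeks, and 42 weeks remain after the interventions end (Measures of health care resource use). The 10-week follow-up comes directly after the last massage (Primary measures of effectiveness) and is ten weeks from randomisation (Sample size and the detectable difference).

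- Nominal end of massage: 52 − 42 = week 10.
- End of massage adverse-event window: 10 + 1 = week 11.
- End of prompt serious-event reporting: week 10.
- Gap: 11 − 10 = 1 week.

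The only interview that asks about adverse experiences is also at week 10, so on this schedule the same week has no planned enquiry after it.

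**3. Dependence on when massage starts**

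The lag L from randomisation to first visit is not given; 0 to 21 days is my assumption. Day 0 is randomisation and the prompt-reporting limit is 10 × 7 = day 70.

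- Ten strictly weekly visits (9 gaps): last visit = L + 63; window ends at L + 63 + 7 = L + 70; gap = L days.
- Visits spread over a full 10 weeks from the first: last visit = L + 70; window ends at L + 77; gap = L + 7 days.

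| L (days) | Weekly: last visit / window end / gap | Full 10 weeks: last visit / window end / gap |
|---|---|---|
| 0 | 63 / 70 / 0 | 70 / 77 / 7 |
| 1 | 64 / 71 / 1 | 71 / 78 / 8 |
| 2 | 65 / 72 / 2 | 72 / 79 / 9 |
| 7 | 70 / 77 / 7 | 77 / 84 / 14 |
| 14 | 77 / 84 / 14 | 84 / 91 / 21 |
| 21 | 84 / 91 / 21 | 91 / 98 / 28 |

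The windows coincide only with strictly weekly visits starting on the day of randomisation. Massage itself passes day 70 only if L exceeds 7 days (weekly visits) or 0 days (full 10 weeks).

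**The case against.** The strongest reply is that the text shows what was meant. Usual care has its own window and the Table 3 row is open to all arms. The serious-event sentence speaks of any adverse event in any participant. On that reading there are two tiers: all serious events go to the DSMB chair, and those possibly due to massage also go to the IRB and NCCAM. This is a sensible scheme and probably the intended one. It stands as evidence of intent, but it works only by setting aside the stated definition, so the wording still needs correcting.

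Three stronger readings are tempting, and the document does not support them.

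- *Massage runs past week 10.* A reader might infer this because the first visit is booked after randomisation. But the plan nominally ends massage by the 10-week follow-up, therapists telephone within 48 hours and are given a deadline for the first appointment, and ten weekly visits fit within 70 days if the first is within 7. Overrun is possible but is not stated.
- *Late serious events are lost.* Only the 7-day report is tied to 10 weeks. Reported adverse experiences still enter the routine DSMB and IRB summaries.
- *The comparison of arms is biased.* Massage participants may be asked up to 10 + 1 = 11 times and usual care once. But no between-arm test of adverse events is planned. The DSMB is to judge unacceptable risk in an arm, not excess over control, so the imbalance distorts no stated analysis.

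It is also fair that this is a condensed article and that the visit forms are not shown. That would excuse missing detail; it does not excuse rules printed together that disagree.

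**Conclusion.** The point holds in two parts. The definition of an adverse experience, with the serious-event wording, contradicts the usual-care window, the unrestricted Table 3 row and the separate causality step; this rests on the text alone. The prompt serious-event window also ends before the massage adverse-event window, by one week on the plan's nominal schedule. The gap is 0 to 21 days with strictly weekly visits and 7 to 28 days with a full 10-week course, under the assumed lag of 0 to 21 days.

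The consequence is limited: delayed rather than absent DSMB reporting, possibly incomplete enquiry in the last days of the window, and uncertainty over what to record in usual care. A reader might go further and conclude that the control arm will show no events. That follows from the literal definition only, and the rest of the section points to an intent to collect them. The wording should be corrected because this is the DSMB's evidence and correction is cheap.

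**What to change.** - Define an adverse event in the same way in all three arms, without requiring relation to massage and without tying seriousness to being on treatment. Record relatedness as a separate item, and use it only for the IRB and NCCAM step.
- Reconcile the windows so that prompt reporting of serious events covers the same period as adverse-event reporting, with a matching period for usual care. Make sure the last enquiry about adverse experiences covers the end of that period.
- If arms are compared on adverse events, use the 10-week interview question common to all arms, and tabulate events reported at massage visits separately.

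The cost is changed wording in the protocol and forms, possibly one moved or added question, and some additional unrelated events to log. Sample size and the efficacy analysis are unaffected.

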#### Stopping rules

The trial will be stopped only if the Data Safety Monitoring Body (DSMB) believes there is an unacceptable risk of serious adverse events in one or more of the treatment arms. In this case, the DSMB could decide to terminate one of the arms of the trial or the entire trial.

We are not proposing to perform an interim analysis for efficacy and therefore have established no formal stopping rules. Even if the two massage treatments reduce pain and dysfunction (the primary outcomes of this trial) more than usual care, we do not consider this an important enough reason to end the trial early. Previous trials of massage have been plagued by small sample sizes and we think it is important that this study be large enough and long enough to clearly evaluate the effectiveness of massage.

### Statistical Issues

#### Sample size and the detectable difference

Because patient function (or dysfunction) is generally considered the more consequential of our two primary outcome measures, we want to ensure that our sample size estimates provide adequate power to detect a clinically significant difference of 2.0 points between groups on the Roland Disability scale [10]. To obtain outcomes data for 120 subjects per group, assuming a 10% loss to follow-up rate, we would need to randomize 133 participants. Our target sample size of 399 randomized individuals (133 per group) was computed using assumptions described below.

To protect against multiple comparisons, we will use Fisher's protected least significant difference approach which has been shown to have desirable properties when there are three groups [23]. This approach makes pair-wise comparisons between the three treatment groups only if the overall F-test is significant. The power of the overall analysis depends on how the means from the three treatment groups differ. We therefore assumed that the FSM group would be one Roland point superior to the RM group, which would, in turn, be one Roland point better than the UC group (giving a difference of 2 points between the FSM and UC groups).

Our estimates of the standard deviations of our primary outcome measures (adjusted for pre-randomization baseline values) derive from analyses of covariance of 8-week follow-up data from 92 study participants in our pilot study evaluating acupuncture for chronic low back pain: Roland SD = 4.65 and Bothersomeness SD = 2.71. Comparable standard deviation estimates at the end of the 10-week treatment period for 83 participants in our pilot study of CAM therapies for chronic low back pain, were 12%-15% lower. Thus, the standard deviation estimates we used for calculating statistical power in the proposed trial are probably conservative, likely underestimating actual power.

With 120 respondents per group (using two-sided significance level of 0.05) the omnibus F-test for the Roland scale will have 85% power for detecting a statistically significant difference among the three treatment means. If this omnibus test is statistically significant, as appears likely given our previous studies of FSM and those of others, we will address each Specific Aim of the study by comparing specified pairs of means, as discussed below. We will have 91% power to detect a pairwise difference of 2.0 Roland units.

For our other primary outcome measure, symptom bothersomeness, we want to be able to detect a minimal clinically important difference of 1.5 points on the 0 to 10 scale [10]. With data for 120 participants per group we will have over 99% power for detecting a minimal clinically significant difference among the three treatment means (assuming they are equally spaced and with 1.5 points between the extremes). In pairwise comparisons we will have 99% power to detect a 1.5-point difference on the Bothersomeness scale.

The power calculations are based on simple comparisons of the follow-up scores at a single point in time (ten weeks after randomization) with adjustment for baseline values using analysis of covariance. We also plan to adjust for other baseline characteristics (e.g., age, gender, and baseline covariates found predictive of 10-week outcomes). Inclusion of such baseline covariates can also improve precision of the variance estimate and therefore increase power.

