**Methods and Design:**

A total of 399 participants (133 in each of three arms) between the ages of 20 and 65 years of age who have low back pain lasting at least 3 months will be recruited from an integrated health care delivery system. They will be randomized to one of two types of massage ("focused structural massage" or "relaxation massage"), or continued usual medical care. Ten massage treatments will be provided over 10 weeks. The primary outcomes, standard measures of dysfunction and bothersomeness of low back pain, will be assessed at baseline and after 10, 26, and 52 weeks by telephone interviewers masked to treatment assignment. General health status, satisfaction with back care, days of back-related disability, perceived stress, and use and costs of healthcare services for back pain will also be measured. Outcomes across assigned treatment groups will be compared using generalized estimating equations, accounting for participant correlation and adjusted for baseline value, age, and sex. For both primary outcome measures, this trial will have at least 85% power to detect the presence of a minimal clinically significant difference among the three treatment groups and 91% power for pairwise comparisons. Secondary analyses will compare the proportions of participants in each group that improve by a clinically meaningful amount.

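### The stated pairwise powers (91% Roland, 99% bothersomeness) ignore the F-test that must come first; in the plan's own Roland scenario the two-step power is about 85%

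*Protocol article*

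**What the plan says.** The section on sample size and the detectable difference adopts Fisher's protected least significant difference for the three arms: "This approach makes pair-wise comparisons between the three treatment groups only if the overall F-test is significant". The Statistical Analysis section repeats the rule, going on to pairs only when an overall difference has been found.

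For the Roland scale the sample-size section assumes that focused structural massage (FSM) beats relaxation massage (RM) by one point and that RM beats usual care (UC) by one point. The SD is 4.65 and the analysis has 120 respondents per arm. On these inputs the overall F-test is given 85% power. The paragraph then ends: "We will have 91% power to detect a pairwise difference of 2.0 Roland units".

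For bothersomeness (SD 2.71, equal spacing, 1.5 points between the extremes) the F-test is given over 99% power, followed by: "In pairwise comparisons we will have 99% power to detect a 1.5-point difference on the Bothersomeness scale".

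The abstract repeats the Roland figures as at least 85% for the three-group comparison and "91% power for pairwise comparisons". Nowhere are the pairwise figures described as leaving the F-test out of account.

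**The concern.** Under the planned procedure a pairwise difference can be declared only if both the F-test and the pairwise test are significant. The probability of both events cannot exceed the probability of either one. If the F-test succeeds 85% of the time, no comparison that waits for it can succeed 91% of the time in the same scenario. For Roland, the two figures in that paragraph therefore cannot both describe the planned procedure under the means assumed there.

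What is at stake is how the trial's power is read. Roland is named as the single most important outcome, and the abstract offers the pairwise figure as a second, higher power beside the 85%. A reader would take the risk of missing a 2-point pairwise difference to be 9%. In the assumed scenario it is about 15%.

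**Working it through.** **Inputs**, all from the sample-size section: two-sided 0.05; 120 analysed per arm, so 360 in all and 357 error degrees of freedom; SD 4.65 (Roland) and 2.71 (bothersomeness); assumed means 0/1/2 (Roland) and 0/0.75/1.5 (bothersomeness).

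**1. The plan's pairwise figures, as stand-alone tests.** The noncentrality is difference / (SD × √(2/120)).
- Roland: 2.0 / (4.65 × √(2/120)) = 3.33, power 91.3% (stated 91%).
- Bothersomeness: 1.5 / (2.71 × √(2/120)) = 4.29, power 99.0% (stated 99%).

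Both reproduce, without any F-test in front.

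**2. The F-test.** The noncentrality is 120 × Σ(mean − grand mean)² / SD², with 2 and 357 degrees of freedom.
- Roland: 120 × (1 + 0 + 1) / 4.65² = 11.10, power 85.3% (stated 85%).
- Bothersomeness: 120 × (0.5625 + 0 + 0.5625) / 2.71² = 18.38, power 97.6%. The plan states over 99%, so here the ceiling is hidden on the page.

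**3. The two-step procedure.** The joint probability was simulated with at least 1 million replicates per configuration. A pair counts only if F is significant and the pairwise t (pooled variance, 357 df) is significant in the right direction.

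| Outcome and pair | Third arm | Two-step power | Stated |
|---|---|---|---|
| Roland, 2.0 points | midway (0/1/2, the plan's scenario) | 84.7% | 91% |
| Roland, 2.0 points | equal to one of the pair (0/2/2) | 89.5% | 91% |
| Roland, 2.0 points | half a point outside (0/2/2.5) | 91.0% | 91% |
| Roland, 2.0 points | one point outside (0/2/3) | 91.3% | 91% |
| Bothersomeness, 1.5 points | midway (0/0.75/1.5) | 97.5% | 99% |
| Bothersomeness, 1.5 points | equal to one of the pair (0/1.5/1.5) | 98.8% | 99% |

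**4. Could 91% be conditional on a significant F-test?** In the plan's Roland scenario the conditional power is 84.7 / 85.3 = 99.3%. So 91% is neither the joint nor the conditional power there.

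**5. Sensitivity to the SD.** The plan reports a second pilot with SDs 12% to 15% lower. With Roland SD 4.65 × 0.88 = 4.09 or 4.65 × 0.85 = 3.95, two-step power for the extreme pair of 0/1/2 is 93.0% or 94.5%. The stand-alone test would then have 96.5% or 97.4%.

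**The case against.** The strongest reply is that the 91% sentence names only a 2.0-point difference and is not tied to equal spacing, which the section introduces for the overall test. Equal spacing is also the least favourable arrangement for a 2-point range. The only 2-point pair in it is FSM against UC, which the Statistical Analysis section says is not a specific aim. If an aim pair (RM against UC, or FSM against RM) differed by 2 points under the hypothesised ordering, the third arm would lie at or outside that pair, and two-step power would be about 89.5% to 91%. This stands. A reader might infer that the type II error for any 2-point pair is 15% instead of 9%; the plan's inputs support that only with the third arm midway. It is about 10.5% with the third arm equal to one of the pair, and about 9% beyond that.

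It can also be said that nothing is concealed, since the rule, the 85% and the 91% stand close together and a careful reader can see the ceiling. That is true for Roland, but no sentence says the 91% leaves the F-test out. Describing the calculations as simple single-time-point comparisons adjusted for baseline does not say so either.

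Finally, the plan calls its SDs probably conservative and expects further covariates to help. That may lift the true power above 91%, but the stated 91% was computed with SD 4.65 and should be right for that SD.

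**Conclusion.** The point holds as a mislabelled power. The 91% and 99% are correctly computed for a stand-alone test, but the trial will apply a two-step procedure. In the one Roland scenario the plan specifies, the procedure's power for the 2-point pair is about 85%. Over the configurations examined, the overstatement runs from nothing to about 6 points for Roland and from about 0 to 1.5 points for bothersomeness.

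The figures rest on 120 analysed per arm, the plan's SDs, normal errors with a common variance, and a single 10-week comparison, as in the plan's own calculation. A reader might infer that the trial is underpowered or needs more participants. The finding does not support that: 85% is the overall power the plan itself set out and accepted, and no test, estimate or error rate changes.

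**What to change.** In the abstract and in the Roland and bothersomeness paragraphs of the sample-size section, do one of two things:

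- State pairwise power for the protected least significant difference procedure, with the configuration of means. For 2.0 Roland points: about 85% in the assumed scenario, and about 90% to 91% with the third arm at or outside the pair. For 1.5 bothersomeness points: about 97.5% to 99%.
- Or keep 91% and 99% and label them as per-comparison powers that do not allow for the preceding F-test.

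If the lower pilot SDs are mentioned alongside, the matching two-step figure for the assumed Roland scenario is about 93% to 94.5%. The cost is a few words and a less favourable headline figure; sample size and analysis stay as they are.

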#### Statistical Analysis

The primary statistical analyses will directly address Aim 1 (to determine if RM is an effective treatment for chronic low back pain) and Aim 2 (to determine if FSM is more effective than RM). A separate analysis will address the third aim, to explore the ability of psychosocial, and clinical baseline characteristics of patients to predict which of them will benefit most from each type of massage and which components of each treatment are associated with superior outcomes. These analyses are described below.

We will use an intent-to-treat approach for all analyses, i.e., individuals will be analyzed by the group to which they were randomized, regardless of participation in any treatment sessions. This minimizes biases that often occur when participants not receiving assigned treatments are excluded from analyses. We will use a standard linear regression mean model (ANCOVA) of the form:

where *Y*(*t*) is the response at follow-up time *t*, *Baseline *is the pre-randomization value of the outcome measure, *Trt *includes dummy variables for the full relaxation massage and focused structural massage groups, *Time *is a series of dummy variables indicating the follow-up times, and *z *is a vector of covariates representing other variables being adjusted for. (Note that α_1_, α_2_, α_3_, and α_4 _are vectors.) The referent group in this model is the usual care group at the first follow-up time. The models will be fitted using Generalized Estimating Equations (GEE) to take into account possible correlation within individuals over time [24]. GEE protects against misspecification of the correlation within a participant's scores over time. Such analyses can incorporate data for every time point at which a patient completes a follow-up interview. However, it is important to first assess whether there is differential dropout by either assigned treatment or symptom or function level. If differential dropout occurs, we will use the method of Little to rectify possible biases that could occur [25].

Both primary outcomes (function and symptoms) will be tested at the 0.05-level, because they address separate scientific questions. Analyses of both outcomes will be reported, imposing a more stringent requirement than simply reporting a sole significant outcome. Arguments against adjusting for multiple comparisons in this situation have been made by Rothman) and others [26-28].

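### Omnibus power for bothersomeness is stated as over 99%, but the plan's own inputs give 97.6%; a minor correction that leaves the design unchanged

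*Protocol article*

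**What the plan says.** All the figures stand in the protocol article under Sample size and the detectable difference.

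- Planning SDs, adjusted for baseline: "Roland SD = 4.65 and Bothersomeness SD = 2.71". A second pilot study gave SDs that "were 12%-15% lower". The article concludes that "the standard deviation estimates we used for calculating statistical power in the proposed trial are probably conservative", so the larger SDs are the ones behind the power figures.
- Level: the Roland calculation is made "using two-sided significance level of 0.05". Under Statistical Analysis the level is not divided between outcomes: "Both primary outcomes (function and symptoms) will be tested at the 0.05-level".
- Testing order: Fisher's protected least significant difference. "This approach makes pair-wise comparisons between the three treatment groups only if the overall F-test is significant".
- Roland: 85% omnibus power for means spaced 0, 1, 2, and 91% pairwise power for a difference of 2.0.
- Bothersomeness: "we will have over 99% power for detecting a minimal clinically significant difference among the three treatment means", for equally spaced means with 1.5 points between the extremes. Then: "In pairwise comparisons we will have 99% power to detect a 1.5-point difference on the Bothersomeness scale".

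The abstract claims less: at least 85% for the three-group comparison and 91% for pairs, on both primary outcomes.

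**The concern.** Two things look wrong in the bothersomeness sentences.

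First, the order of the two powers. The Roland figures put omnibus power below pairwise power. The bothersomeness figures put it at or above pairwise power. Both outcomes use the same layout: three groups of 120, equally spaced means, and a pairwise difference equal to the full spread. The order should therefore be the same.

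Second, the size. If the omnibus figure does not follow from the SD printed in the section, the plan states a power that the design does not have under its own assumptions.

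The omnibus test matters because it is the gate to the pairwise comparisons that answer the trial's aims for this outcome. What is at stake here is the accuracy and internal consistency of one planning figure.

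**Working it through.** **Inputs** (all from the protocol article): 120 analysed per group, three groups; SD 2.71 for bothersomeness and 4.65 for Roland; level 0.05, two-sided; means 0, 0.75, 1.5 for bothersomeness and 0, 1, 2 for Roland; a single time point at 10 weeks with baseline adjustment.

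**Formulas**

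- Omnibus: λ = n × Σ(μᵢ − μ̄)² / SD². Power is the probability that a noncentral F with 2 and 357 degrees of freedom (3 × 120 − 3) and noncentrality λ exceeds the 5% critical value, 3.02.
- Pairwise: δ = d / (SD × √(2/n)). Power comes from the noncentral t, or from its normal approximation.

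**Step 1: reproduce the figures that agree**

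| Figure | Noncentrality | Recomputed | Stated |
|---|---|---|---|
| Roland omnibus | λ = 120 × (1² + 0 + 1²) / 4.65² = 11.10 | 85.3% | 85% |
| Roland pairwise, 2.0 points | δ = 2 / (4.65 × √(2/120)) = 3.33 | 91.3% (normal: 91.5%) | 91% |
| Bothersomeness pairwise, 1.5 points | δ = 1.5 / (2.71 × √(2/120)) = 4.287 | 99.0% | 99% |

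The method and the SDs are therefore those of the plan.

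**Step 2: the figure in question**

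λ = 120 × (0.75² + 0 + 0.75²) / 2.71² = 120 × 1.125 / 7.3441 = 18.38.

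Power = 97.6% by the noncentral F. The chi-square approximation gives 97.7% and a simulation of 200,000 trials gives 97.6%. Taking one further degree of freedom for the baseline covariate leaves it at 97.6%. The plan states over 99%.

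**Step 3: the ordering, which needs no software**

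With equal spacing and a spread of d, Σ(μᵢ − μ̄)² = 2 × (d/2)² = d²/2, so λ = n d² / (2 SD²). For the two extremes, δ² = d² / (SD² × 2/n) = n d² / (2 SD²). The two are identical: for bothersomeness, 4.287² = 18.38. The F-test spreads the same noncentrality over two degrees of freedom and the t-test over one, so at the same level the F-test has less power. Omnibus power above 99% is therefore incompatible with pairwise power of 99% when n and SD are the same.

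**Step 4: can another reading reach 99%?**

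| Change to the inputs | Omnibus power |
|---|---|
| All 133 randomized per group analysed | 98.6% |
| Level 0.10 | 98.9% |
| SD 12% lower (2.385) | 99.5% |
| SD 15% lower (2.304) | 99.7% |
| Means 0, 0, 1.5 (not equally spaced) | 99.6% |

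With equal spacing, 99% is reached only at an SD of about 2.50 or less, at about 141 per group, or with about 1.63 points between the extremes. None of these is what the sentence assumes.

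**The case against.** The strongest reply is that the gap is immaterial. A difference of 1.4 points lies within the 2 points commonly tolerated when a power figure is reproduced, and both values describe a test that is very likely to succeed. Nothing was built on it: the 133 per group was derived from the Roland scale, which the article calls its most important outcome, and 97.6% clears the abstract's 85% easily. The article also expects its SDs to understate power and notes that further covariates may add some.

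Most of this stands, and it limits the weight of the point. It does not make the sentence right. The plan states a lower bound, and the bound is not met on the inputs given. A tolerance on size also does not excuse the impossible order of the two bothersomeness powers. The possible gains from a smaller SD or more covariates are offered as reassurance beyond the calculation, not as inputs to it.

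A reader might infer that the authors used the lower pilot SDs for this one figure and the higher ones elsewhere. The documents do not support that. The SD needed for 99% is 2.50, about 8% below 2.71, so the SDs that are 12% to 15% lower clear the threshold rather than match it. Had they been used in the same paragraph, the pairwise power would be 99.8% to 99.9%, not 99%. Other slips fit equally well, such as two equal means with the third 1.5 points away (99.6%), or loose rounding.

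**Conclusion.** The point holds as a minor numerical correction. On the stated inputs (120 per group, SD 2.71, level 0.05, equally spaced means with 1.5 points between the extremes), the omnibus power for bothersomeness is 97.6%, at least 1.4 percentage points below the stated bound, and it must lie below the 99% pairwise figure. The result rests on the usual equal-variance, single-time-point calculation that the article describes, and that calculation returns its other three figures.

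The sample size, the analysis, the testing order and the abstract's power claim are unaffected. How the figure arose cannot be told from the article.

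A reader might also be tempted to express the gap as a multiple of the chance of missing the omnibus gate. That would overstate it. In absolute terms the chance is 2.4% rather than under 1%, while the plan openly accepts about 15% (100% − 85%) for the Roland scale, and the conclusion that bothersomeness is amply powered does not change.

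**What to change.** In Sample size and the detectable difference, give the omnibus power for bothersomeness as about 98% (97.6%) in place of over 99%, and leave the 99% pairwise figure as it is. All four power figures then follow from the stated SDs and stand in the right order. The cost is one figure in the text, slightly less favourable than before; no change to the sample size, the analysis or the abstract follows.
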